| Informed Consent |  |
| Informed consent will be obtained from the patient after a qualified study team member explains the study and the patient has fully understood the study. The informed consent form is in a written format and will be explained orally by the qualified study team member to the potential patient in English with the presence of a witness. A translator will be present if the patient does not understand English. In addition, the translated short consent form will be used based on the patients’ preferred language. Sufficient time for the patients to review and consider participating will be given. "Your participation in this study is voluntary. You may stop participating in this study at any time. Your decision not to take part in this study or to stop your participation will not affect your medical care or any benefits to which you are entitled." is stated on the Patient Information Sheet and will be explained to patients. |  |
| IRB review |  |
| NUH has oversight purview over this study and will submit the protocol and the associated informed consent documents for the review and approval by the NHG DSRB.  This study will be conducted in accordance with the ethical principles that have their origin in the Declaration of Helsinki and that are consistent with the Good Clinical Practice and the applicable regulatory requirements.  This final study protocol, including the final version of the Patient Information Sheet and Informed Consent Form, must be approved in writing by the Cluster Ethic Review Board: DSRB prior to enrolment of any patient into the study.  The PI is responsible for informing the Cluster Ethic Review Board: DSRB of any amendments to the protocol or other study-related documents, as per local requirement. |  |
| Confidentiality of Data and Patient Records |  |
| The Principal Investigator and study team will be fully trained and will conduct the project strictly based on data protection and compliance policy according to institutions’ and ethic regulation. The patient records and de-identified blood samples will be separately coded and stored for maintaining patients’ confidentiality. All files are password protected and stored on secured servers with limited access.  However, there is still a potential risk of data breaching as data collection is involved. |  |
|  |  |
| **PUBLICATIONS** |  |

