| Patients who meet any of the following prerequisites will not be allowed to take part in this study:   - Women who are currently pregnant or breastfeeding - Cognitive impairment which prevents the patient from giving voluntary consent - History of any psychiatric conditions such as depression, psychosis, schizophrenia etc. - History of cancer in the past 5 years - History of abnormal renal or liver function - History of diabetes mellitus - Hepatitis B and/or Hepatitis C carrier - Diagnosed with tuberculosis (Positive microbiological evaluation for Grocott Methenamine Silver stain and Ziehl– Neelsen stain) - Any immunosuppressants or anti-inflammatory medications such as NSAIDS for the past 3 months - Concomitant medication that may have contraindication with prednisolone and methotrexate use |  |
| Withdrawal Criteria |  |
| Patients will be withdrawn from the study upon their request. However, data that has been collected until the time of withdrawal will be kept and analysed.  In cases of persistent non-compliance to dosing or study procedures, the data on non-compliance will be recorded, and the outcomes will be analysed based on intention-to-treat.  Under the following circumstances, patients will continue to be retained in the study to collect outcome data, but will be discontinued from taking the study drug:   - Serious allergic reaction to study drug requiring medical intervention and/or hospitalisation and as decided by investigators for safety reasons - Development of adverse drug reactions to the prescribed trial drugs which require medical intervention and as decided by investigators for safety reasons - Needing ventilator support upon hospitalisation, which prevents the consumption of tablets orally |  |
| Subject Replacement |  |
| There will be no replacement for patients who withdraw during the treatment period. |  |
|  |  |
| **4. TRIAL SCHEDULE** |  |

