| *Screening*  After patient is consented to the study, a baseline blood test (32mls, including pregnancy test, Hepatitis B test, Hepatitis C test, full blood count, liver function test and renal function test) and chest X-Ray will be conducted during the baseline visit to assess for eligibility prior to enrolment to the treatment phase. Additional research blood (14.5mls, 1 tablespoons) will be collected at this baseline visit for research purposes. Patient may be exempted from chest X-Ray and/or blood test if patient has done the same test within 30 days.  Baseline demographics and relevant clinical variables of patients will be collected. The following demographic and clinical variables will be collected: age of presentation, pre-menopausal or post-menopausal status, parity / breastfeeding status, concomitant rheumatic conditions, personal or family history of tuberculosis, smoking or alcohol intake, presenting complaint, unilateral or bilateral involvement, affected quadrant of the breast, duration of symptoms and previous antibiotics prescription for treatment of IGM.  Information on comorbidities will be evaluated to ensure suitability for both treatment arms prior to recruitment. Examples include drug allergies, plans for pregnancy, ongoing infection, previous history of cancer, previous tuberculosis, epilepsy, diabetes, hypertension, kidney, liver, cardiac problems, osteoporosis, glaucoma, peptic ulcers, previous side effects to either prednisolone or methotrexate.  If patient fulfilled all the eligibility criteria after screening assessment, she will be randomised to either of the treatment arm.  If patient did not meet the full eligibility criteria (eg. Pregnant, hepatitis carrier or abnormalities in renal or liver panels), she will not proceed to the treatment phase. The data collected and additional blood samples will be kept for analysis.  *Treatment Phase*  Patient will be scheduled to attend a clinical visit (T_0_) to either breast or rheumatology clinic if she meets all eligibility criteria for the initiation of treatment dose. There will be a window period of ± 7 days for this clinical visit. Patient is required to complete a pre-treatment quality of life online survey (approximately 10-15 minutes).  Patient will be scheduled for blood test (8mls, 0.5 tablespoons) and clinical visits to either breast or rheumatology clinic at the 1^st^ (T_1_), 2^nd^ (T_2_), 3^rd^ (T_3_) and 6^th^ (T_4_) month to assess their signs and symptoms, and drug compliance. There will be a window period of ± 14 days for each of these clinical visits. Additional research blood (14.5mls, 1 tablespoons) will be collected on the 1^st^ (T_1_) and 6^th^ (T_4_) months.  Patients are required to undergo a breast ultrasound to assess for their radiological response during the 3^rd^ (T_3_) clinical visit. A window period of ± 14 days will be applicable. The initial measurement of the breast lesion or mass will be recorded in three dimensions – i.e. anteroposterior, superior-inferior, mediolateral measurements. If complete clinical and radiological complete response has been achieved on the 3^rd^ (T_3_) visit, the doctor will discontinue the drug in a safe manner and no further breast ultrasounds will be required. If the patient’s symptoms or signs have not resolved by the 3^rd^ (T_3_) clinical visit, patient’s drug dosage will be assessed by the rheumatologist and treatment may be continued up to the 6^th^ (T_4_) month period and a repeat breast ultrasound will be required at the 6^th^ (T_4_) month. If symptoms have not resolved by the 6^th^ (T_4_) month of clinical visit, the patient’s drug dosage may be up-titrated or will be given an addition of a second therapy, i.e. combination therapy of steroid and methotrexate may be used. For clinical visits mention above, it will coincides with standard care visit.  During the clinical visits, Tingting Hu et al’s “M- score” will be adopted to grade the severity of the disease. M score is being calculated during clinical visits for IGM patients regardless of trial status for objective follow up. This is a common practice. For this study, the score will be administered by their attending healthcare professional (not limited to breast surgeons, investigators, or breast care nurses).  The M-score will be the sum of the following:  1) Mass score  2) Erythema score  3) Fistula score  4) Pain score  5) Quality-of-life (QoL) score  The scoring criteria were defined as follows:  1) Mass score: 0 for the absence of mass by palpation; 1 for mass ≤3 cm by palpation; 2 for mass >3 cm by palpation.  2) Erythema score: 0 and 2 for the absence and presence of erythema, respectively  3) Fistula: 0 and 2 for the absence and presence of fistula, respectively  4) Pain Score: 0 for Visual Analogue Score (VAS) 0-2; 1 for VAS 3-5; 2 for VAS 6-10  5) QoL score: 0 for absence of effects on QoL; 1 for mild effects on QoL, where the patient does not require medical assistant; 2 for serious effects on QoL, where the patient requires medical assistant  The total M-score ranges between 0 and 10 and serves as a quantitative and objective measurement of the severity of the symptoms.  The primary endpoint will be the clinical complete response (cCR) rate, which is defined as the proportion of patients who have an M-score of ≤ 1 at ≤1 years after treatment.  The secondary endpoints will be as follows:   - - The time to cCR, defined as the median time to cCR post randomisation.   - The treatment failure (TF) rate, defined as the proportion of patients with TF at 1 year post randomisation. The TF status will be defined as follows:     - If the patient has an M-score ≥6 before randomisation, TF is defined as the M-score remaining at ≥6 at 1 month post randomisation.     - If the patient has an M-score between 4 and 5 before randomisation, TF is defined as the M-score remaining at ≥4 and never being lower than 4.     - If the patient has an M-score <4 at baseline but never reaches cCR after randomisation, TF is defined as the M-score being >5 at the follow-up and remaining above 5 for one month. - Relapse rate, which is defined as the proportion of patients who have M-score >4 among the patients who achieved CR.   Throughout the course of the study, there are possible flares and relapse of the disease. Flares will be defined as any increase in M-score or lesion size on ultrasound whilst on therapy. While relapse will be defined as recurrence of symptoms or signs of IGM in the breast after previously experiencing complete resolution following therapy. If relapse occurs, patient will restart the same treatment arm for 6 months.  In the event of flares, blood test (8mls, 0.5 tablespoons) and additional research blood (14.5mls, 1 tablespoons) will be collected and the allocated treatment for the patient will be up-titrated by the doctor. In event of relapse, treatment for the patient will be reinitiated as per the allocated arm.  Additional research blood samples collected during the trial will be used for gene expressing profiling to identify unique patterns of gene expression that can be used to diagnose IGM and predict its treatment response.  Regardless of treatment arm, patient will be monitored by either breast surgeon or rheumatologist. Surgeons will assess for eligibility into trial, clinical reviews, and ultrasound breasts interpretation. Rheumatologists will be monitoring for drug side effects and titration if required. In event of failure of medical therapy, surgeons will have to intervene accordingly for aspiration or surgical drainage. In the event where patients require aspiration or surgical drainage during the study, methotrexate or prednisolone should be continued unless there is evidence of sepsis. The frequency of aspiration or surgical intervention will be recorded as events during the study.  Whenever the disease has been resolved during the study period, the balance medication and/or packaging will be retrieved to do medication accounting and checking for adherence to assigned treatment arm.  If side effects were to develop, doctors will evaluate the severity of the side effects and withdraw the patients from the trial if needed. |  |

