| *Follow up Phase*  The last clinical visit at the 12^th^ (T_5_) month may be a physical clinical visit or teleconsultation, depending on the doctor’s decision. Patient will be asked to complete a post-treatment quality of life online survey (approximately 10-15 minutes) during this visit. There will be a window period of ± 30 days for the last clinic visit. Please refer to Figure 1 for the study timeline. |  |
| **iii. Post Study Follow up and Procedures** |  |
| If there are any unresolved adverse events that require medical intervention, follow-up visits will be conducted and verified through the electronic medical records of their hospitalisation.  In the case of serious adverse events, this will be reported to the DSRB as soon as possible, no later than 7 calendar days after first knowledge by the investigator, and any additional relevant information about the event should be reported within 8 calendar days of making the initial report.  Patients’ clinical information and personal data may be combined or linked with, including but not limited to: government administrative data and research data such as, nation-wide health-related databases, economic data and National Autoimmune Registry, up to 31 December 2043. The linkage may be carried out by itself or with the assistance of a data intermediary. The collection of such data is for the purposes of the current research study and will be collected prospectively. |  |
| **iv. Discontinuation Visit and Procedures** |  |
| A discontinuation visit will be conducted for all patients who discontinued the study drug or withdrawn from the study regardless of whether it is voluntary based on patient’s request or decided by the Investigators for safety or non-compliance issues to follow-up on:   - Balance medication and packaging retrieval to do medication accounting and checking for adherence to assigned treatment arm - Existing AE(s) /SAE or complaints that are not resolved and to ensure that care assessment with support care delivery is continued until the problem is resolved. - Reason for withdrawal (if requested by the patient) |  |
| **TRIAL MATERIALS** |  |
| Trial Product (s) The investigational product (IP) and Auxiliary Product (AP) will be procured locally from NUH pharmacy and stored at NUHS Investigational Medicine (IMU) facility. |  |

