| **UPIRTSO events** refers to problems, in general, to include any incident, experience, or outcome (including adverse events) that meets ALL of the following criteria:   1. **Unexpected** 2. Pregnancy   In the event that the patient becomes pregnant during the study period, although very unlikely (patient will be screened for pregnancy before treatment phase and checked for pregnancy status at each clinical visit), patient will be withdrawn from the trial immediately. However, patient will be advised by their doctor or study investigator(s) on the procedures to stop medication.   1. Cancer   In the event that the patient is diagnosed with cancer during the study period, patient will be withdrawn from the trial immediately. However, patient will be advised by their doctor or study investigator(s) on the procedures to stop medication.   1. Fall risks   In the event that the patient falls during the treatment phase due to the side effect, doctor or study investigator(s) will assess and evaluate the severity of the fall before advising on the continuation of the study drug.  Expedited reporting to the IRB will be done as soon as possible, and not later than 7 calendar days after first knowledge by study investigator(s).   1. **Related or possibly related to participation in the research**   Prednisolone may cause mood changes (confusion, depression), weight gain, fluid retention, nausea, vomiting, indigestion, easy bruising, blood or black, tarry tools, blurred vision, increased urination or thirst, muscle weakness or cramps and severe stomach pain.  Methotrexate may cause mouth ulcers, nausea, vomiting, abdominal pain, diarrhoea, rash, hair loss, easy bruising, severe sore throat, tiredness, paleness, yellow eyes, tea-coloured urine, constant abdominal pain, risk of infection and breathlessness or persistent dry cough.   1. **Risk of harm**   Both prednisolone and methotrexate have been widely used clinically for treatments of other diseases and have a good safety profile.  The study investigators will make every effort to mitigate risks and ensure that the inclusion and exclusion criteria are strictly adhered to. Study investigators will also conduct close monitoring on the patients’ well-being during the clinical visits.  **Reporting Timeline for UPIRTSO Events to the NHG DSRB.**   1. Urgent Reporting: All SAE(s) listed whether related to or not to the study will be reported to IRB within 24 hours after first knowledge by study investigator(s):  - Results in death. - Is life-threatening (immediate risk of death). - Requires inpatient hospitalization or prolongation of existing hospitalization. - Results in persistent or significant disability/incapacity. - Is a medically important event.  1. Expedited Reporting: All collected study AE(s) will be reported as soon as possible, but not later than 7 calendar days after first knowledge by the study investigator(s). |  |

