| De-identified blood samples will be analysed and stored in NUH Tissue Repository. Recruitment and follow-up survey data will be collected electronically via NUHS REDCap. Only study team members with delegated rights will be able to access the data under the supervision of PI and Site-PI. All survey data will be collected electronically via FormSG. A copy of de-identified data will be stored in a secured server at NUH. |  |
|  |  |
| **SAMPLE SIZE AND STATISTICAL METHODS** |  |
| Determination of Sample Size |  |
| The prevalence rate of IGM in NUH is currently at 10 to 15 patients per year. Based on a stepped rule of thumb, a minimum sample size of 30 will provide at least 80% power to detect a medium standardised effect size of between 0.3 to 0.7 based on a randomised two-group comparison (Machin et al, 2021). Assuming a 20% attrition rate, the sample size required for this study is 36 patients. This will be rounded up to a sample size of 40 patients over a period of 36 months. |  |
| Statistical and Analytical Plans The primary outcome of 6-month clinical or radiological complete response will be compared between arms using Chi-square test. The effect estimate will be quantified in terms of difference in proportion as well as relative risk (RR) and their associated 95% confidence interval (CI). The secondary outcomes of time-to clinical or radiological response and time-to-relapse will be evaluated via the Kaplan-Meier method. The differences in survival curves will be compared using log rank test, with the effect estimate quantified in terms of hazard ratio and its 95% CI. The primary analysis of this trial will be based on Intention-to- Treat (ITT). A Per Protocol (PP) analysis will be performed on all patients who have completed 6 months of treatment regimen as a sensitivity analysis.  Chi square test will be used to evaluate the proportion of side effects and requirement for percutaneous or surgical intervention during treatment between arms. Modified Poisson regression will be used to identify clinical or biomarkers that are associated with treatment response and quantify the effect in terms of RR.  Patient reported outcomes will be reported via a survey on FormSG, conducted online. The questions will be adapted from SF36 V1 Singapore version and EORTC-BR23. Below are the domains to be compared:   - - General Health   - Physical Health   - Mental Health   - Body Image   - Sexual Image   - Breast Health |  |
| **ETHICAL CONSIDERATIONS** |  |

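### For women who withdraw at their own request, the protocol provides for no later outcome data and no M-score at the discontinuation visit, although the M-score is taken in routine care

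*Protocol*

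**What the plan says.** Protocol 3.5 (Withdrawal Criteria) treats three groups differently.

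- **Withdrawal at the patient's request:** "data that has been collected until the time of withdrawal will be kept and analysed". Nothing is said about outcomes after that date.
- **Persistent non-compliance:** it is recorded, and "the outcomes will be analysed based on intention-to-treat".
- **Study drug stopped** for a serious allergic reaction, an adverse drug reaction needing medical intervention, or ventilator support: "patients will continue to be retained in the study to collect outcome data".

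Two other places use trial withdrawal where 3.5 might have led the reader to expect retention. On side effects, 6.3 says "doctors will evaluate the severity of the side effects and withdraw the patients from the trial if needed". On pregnancy and on cancer, 9.2 says "patient will be withdrawn from the trial immediately". Neither mentions outcome data afterwards.

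Section 6.3 iv states: "A discontinuation visit will be conducted for all patients who discontinued the study drug or withdrawn from the study". Its list covers medication accounting, unresolved adverse events or complaints, and the reason for withdrawal. It names neither an M-score nor an ultrasound.

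On routine care, 6.3 states: "M score is being calculated during clinical visits for IGM patients regardless of trial status for objective follow up". It adds that the visits described up to that point, which run to month 6, coincide with standard-care visits.

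The primary analysis is by intention to treat (11.2). Withdrawals are not replaced (3.6). The sample size is set "Assuming a 20% attrition rate" (11.1).

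**The concern.** An intention-to-treat comparison needs an outcome for every randomised woman. The protocol makes no provision for later outcomes from women who withdraw by choice, although the clinical component may be recorded in the same hospital's clinics anyway. The trial is open label (8.5), and fewer side effects with methotrexate is part of the hypothesis (2.1). Withdrawal could therefore plausibly differ between arms and be related to outcome, which is when missing values bias the comparison.

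This is a protocol matter. An analysis plan can choose how to handle missing values, but it cannot collect them or obtain a woman's agreement to their use. The unreconciled wording adds to the problem: a woman with a troublesome adverse reaction is retained for outcomes if 3.5 is followed, and may be withdrawn from the trial altogether if 6.3 is followed.

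**Working it through.** **Inputs.** From the protocol: minimum size 30, attrition 20%, inflated size 36, final size 40 (11.1); 20 per arm (5.1). Assumed here: attrition occurs at exactly the planned rate and splits equally, 4 per arm.

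**The plan's own figure.** 30 × 1.2 = 36, as stated. Dividing by the retained fraction gives 30 / 0.8 = 37.5, rounded up to 38. The final 40 covers both.

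**Expected loss.** 0.20 × 40 = 8 women missing and 32 observed, still above the plan's minimum of 30.

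**Effect on the primary comparison.** Let x be the responders observed and m the number missing in each arm of 20.

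- Lowest risk difference: x(MTX)/20 − [x(Pred) + m(Pred)]/20
- Highest risk difference: [x(MTX) + m(MTX)]/20 − x(Pred)/20
- Width: [m(MTX) + m(Pred)]/20 = (4 + 4)/20 = 0.40, or 40 percentage points, whatever the observed rates

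Illustration with assumed results of 8/16 on prednisolone and 12/16 on methotrexate:

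- Observed difference: 0.75 − 0.50 = 0.25
- Lowest: 12/20 − 12/20 = 0.00
- Highest: 16/20 − 8/20 = 0.40

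**Effect on precision.** The standard error rises by √(20/16) = 1.118, about 12%. At assumed rates of 50% and 75%, the 95% interval half-width is 1.96 × √[(0.25 + 0.1875)/n], which is 0.29 at n = 20 and 0.32 at n = 16 per arm.

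**What recovery could achieve.** The protocol does not say how much of the 20% is voluntary withdrawal, nor how many such women would keep attending clinic and agree to record use. Over the whole range of the recoverable share:

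| Share recovered (assumed) | Women recovered | Still missing | Width of bounds |
|---|---|---|---|
| 0% | 0 | 8 (20%) | 40 points |
| 25% | 2 | 6 (15%) | 30 points |
| 50% | 4 | 4 (10%) | 20 points |
| 75% | 6 | 2 (5%) | 10 points |
| 100% | 8 | 0 | 0 points |

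The width is the number still missing divided by 20. The table counts a recovered M-score as settling the outcome. That is so for the endpoint in 6.3 (M-score ≤1). For the outcome in 11.2 (clinical or radiological complete response at 6 months), a score of 1 or less near month 6 establishes response, while a higher score leaves the radiological part open. For 11.2 the widths are therefore optimistic.

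**The case against.** The strongest reply is that 3.5 already separates stopping drug from leaving the trial for listed safety reasons, and analyses non-compliers by intention to treat. That stands. A reader might infer that outcome collection ends for everyone who discontinues; the document does not say so. The gap is confined to withdrawal on request and to the cases in 6.3 and 9.2 where retention is not stated.

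A reader might also infer that a fifth of the primary outcomes will be lost needlessly. The documents do not support this. The 20% is an all-cause planning allowance, never attributed to voluntary withdrawal, and the planned 40 absorbs it in numbers. Women who stop attending will have no routine score, and women who refuse record use cannot be included.

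Nor can it be assumed that month-6 and month-12 scores will already be on file. No routine visit schedule is given for withdrawn women. The standard-care statement reaches only to month 6. The month-12 visit may be a teleconsultation (6.3), whereas the mass component is scored by palpation.

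The radiological part would indeed be missing. This weighs less than it seems, because Figure 1 leaves the month-6 ultrasound to the doctor's discretion, and the text of 6.3 requires it only if symptoms or signs had not resolved by month 3.

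An M-score at an early discontinuation visit is not a 6-month outcome, and one may be taken there anyway if the visit is in clinic. Both points are fair. Listing it makes its collection definite and gives a last observed value for the time-to-event outcomes.

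Finally, the consent form is not available, so it may already offer partial withdrawal. Handling of missing data may be in an analysis plan not shown, so it cannot be said that the analysis will use only women who stay. Neither point supplies the missing provision in 3.5.

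**Conclusion.** The point holds in a limited form. For voluntary withdrawal, the protocol provides for no later outcomes and lists no M-score at the last visit, while describing a routine source from which some could be obtained. Sections 6.3 and 9.2 also leave it unclear whether outcome data continue after withdrawal for side effects, pregnancy or cancer, and must be reconciled with 3.5.

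At the planned attrition, 8 of 40 outcomes are missing and the bounds on the risk difference are 40 points wide. Recovery could remove anything from none to all of that for the M-score endpoint, and probably only part in practice. The size rests on attrition at exactly 20%; the width does not depend on the observed rates or on how the 8 divide between arms. This is a worthwhile, inexpensive improvement to data collection and does not show that the trial's result would be wrong.

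**What to change.** 1. In 3.5, and in the consent form if it does not already do so, distinguish three decisions: stopping study drug, stopping study visits, and refusing further use of clinic records. Stop outcome collection only on the third.
2. At withdrawal, ask for agreement to use the routine-care M-score nearest month 6, and nearest month 12 where one exists. Use these values in the intention-to-treat analysis, with the actual date recorded.
3. Add an M-score to the list in 6.3 iv. State that it serves as a last observed value for time to response and relapse and does not replace the 6-month outcome.
4. Reconcile the side-effect sentence in 6.3 and the pregnancy and cancer text in 9.2 with 3.5, so that each says whether outcome data continue to be collected. The clinical decision itself is not at issue here.

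The cost is protocol and consent wording plus one score at a visit already planned. The drawbacks are that routine scores may fall outside the ±14-day window, will not exist for women who stop attending, depend on the woman's agreement, and give only the clinical part of the clinical-or-radiological outcome.
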